### Method of randomization

Randomization is performed by the NTNU web-CRF solution with separate blocks and stratification to age and gender for each collaborating hospital.

(https://webcrf.medisin.ntnu.no/client/index.php). Randomization of a new patient in one of the participating hospitals will generate a coded message to the project group with information of treatment and inclusion number for this hospital.

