Although numerous studies exist dealing with proximal humeral fractures, most of them represent level IV evidence [15]. Thus, interpretation must be made with caution and evidence is at present too limited to support secure recommendations for treatment, even including if surgical treatment is superior to conservative for severely displaced fractures. The number of level I and II trials in this field are few. In our department we recently completed a single center randomized controlled study of displaced proximal humeral fractures; an angular stable plate was compared to conservative treatment. After two years follow-up we could not detect any significant differences between surgery and conservative treatment with regard to physical functioning and health-related quality of life [16, 17]. Nevertheless, there is evidence that the rate of surgical treatment has increased significantly in the period from 1999 to 2005 [18].

The proximal humeral fracture groups comprise two-, three,- or four part fractures: non-displaced, displaced or displaced with dislocation (AO-OTA type A,B and C) [19]. Many proximal humeral fractures are minimally displaced, and should not be considered for surgical treatment. About one fifth are displaced 3- and 4 part fractures (AO-OTA group B2 and C2) [7]. In these fractures many surgeons perform operative treatment, even if this has not been proven superior to a conservative approach except from in certain displaced fracture dislocations, where surgery may be favorable [3]. However, most orthopaedic surgeons agree that classification and differentiation of the main groups of proximal humeral fractures are important for treatment decision making, as prognosis and the technical challenges depend on the fracture displacement and comminution [20, 21].

If surgery is decided, the most frequent treatment modalities are open reduction and internal fixation with an angular stable plate, a locked intramedullary nail, or in some patients minimally open surgery with screws, threaded pins and sometimes cerclage wires. Shoulder hemi-artroplasty has also been widely used [22–32]. Although numerous surgical options exist for the displaced fractures, none has yet proven to be superior [3, 33–35]. Also, several complications and impaired shoulder function are reported after different types of surgical treatment [36–43].

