### The inclusion criteria

Patients aged 65 or older admitted to hospital with a displaced three- or four part proximal humerus fracture of OTA/AO group 11-B2 or 11-C2 (displaced fracture of extra-articular or articular, bifocal type) [19]. The subgroups -.1, -.2 and -.3 will be included for both B2 and C2 groups, provided severe displacement, defined as a mal-position of at least 45° of angular deviation in valgus or 30° in varus in true frontal projection, regardless of whether the fracture is impacted or not. Fracture with more than 50% displacement of the head against the metaphysis (surgical neck) will also meet the criteria. The greater or lesser tubercles must be displaced in a three- or four part fracture, the degree of displacement is not critical for inclusion.

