### Statistics

Statistical analyses will be performed with the SPSS 17.0 software or later version (SPSS Inc. Chicago, Illinois, USA). All outcomes will be reported as mean values and 95% confidence interval (95% CI) for both treatment groups and for each hospital separate, as well as for all hospitals together. In case of small data groups, bootstrapped 95% CI will be calcluated. Mean differences between the groups will be compared with independent *t*-test and Mann–Whitney test as appropriate at two and five years follow-up. Subgroup analyses for the two fracture groups B2 and C2 are planned to gain further information of effectiveness of treatment. Multiple imputation will be used to handle missing values. The QALY analysis from 15D outcome will be performed according to the specific 15D syntax for SPSS and completed with a one-way sensitivity analysis for each variable in the analysis.

The intention-to-treat principle will be adopted: Patients will be analysed according to their initial treatment group in case of cross over to the other group.

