Concerning the surgical treatment, not all parts of the treatment can be standardized, and may represent confounders. For the ORIF procedure the different fracture patterns, as well as the use of a medial calcar butress plate, may confound outcome. However, the surgeons perioperative individual judgement of the technically best treatment solution will have priority. All adjuvant treatment in addition to the Philos plate and thread cerclages around the tubercles will be reported.

Current recommendations in the litterature advise the use of reversed total shoulder arthroplasty in patients aged over 70 years [37]. Even so, the lower age limit in this trial has been set to 65 years. An acute proximal humeral fracture clearly represents a different problem compared with a planned revision of a failed arthroplasty or sequela after a malunited fracture. Kaplan-Meier survivorship analysis has showed acceptable outcomes for cuff tear arthropaties, while revision arthroplasties and fracture sequelae show less favourable results after 8–10 years [78, 79]. Primary joint replacement after fracture of the proximal humerus has gained better results than secondary revision arthroplasty, and hemi-arthroplasty give less predictable results than RTSA [39]. Thus, the youngest patients group in this trial may obtain a more predictable shoulder function for the next 8–10 years after a RTSA compared to using other prosthetic modalities. Therefore a potential decline in QoL will be delayed and possibly minimized, as older persons usually will have a natural decline in shoulder function and lower demand with higher age.

Some ongoing and recently completed trials deals with the issue of best treatment of proximal humeral fractures. Two recent randomized controlled trials of four-part humeral fractures treated either non-operatively or with hemiarthroplasty, could not show differences between the treatment groups at one year [80, 81]. Neither could our former trial comparing ORIF and non-operative treatment for three- and four part fractures prove any difference in favor of one of the treatments [16, 17].

However, no study has yet, to our knowledge, compared RTSA and ORIF. The only known trial comparing RTSA with another surgical option, is a small level 3 study, concluding that RTSA outperformed hemi-arthroplasty with regard to all outcomes measures assessed [57].

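### Fracture group (B2 or C2) is treated as important to outcome but is neither a stratification factor nor a covariate in the stated unadjusted comparison; adjusting for it would gain some precision

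*Protocol article*

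**What the plan says.** **Eligibility.** The inclusion criteria accept a "displaced three- or four part proximal humerus fracture of OTA/AO group 11-B2 or 11-C2" and add: "The subgroups -.1, -.2 and -.3 will be included for both B2 and C2 groups, provided severe displacement". Extra-articular and articular fractures therefore enter the same trial.

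**Importance of fracture type.** The Background says that "prognosis and the technical challenges depend on the fracture displacement and comminution". The Discussion says: "For the ORIF procedure the different fracture patterns, as well as the use of a medial calcar butress plate, may confound outcome". The operative technique section links late screw penetration, caused by sinking of the head, to intracapsular C-type fractures.

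**Randomisation.** Allocation uses "separate blocks and stratification to age and gender for each collaborating hospital". Under Method of inclusion, radiographs are classified locally and confirmed at the study centre before randomisation, so a fracture group is on record when a patient is allocated.

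**Analysis.** The Statistics section compares mean differences at two and five years by independent t-test or Mann-Whitney test and names no covariate. It also states: "Subgroup analyses for the two fracture groups B2 and C2 are planned to gain further information of effectiveness of treatment".

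**The concern.** The document singles out fracture type three times: as a determinant of prognosis, as a possible confounder on the plate side, and as the basis of its only named subgroup analysis. Neither the allocation nor the stated test then makes use of it. If B2 and C2 patients differ in outcome, two things follow. A chance difference between arms in the share of C2 fractures moves the unadjusted estimate in that particular trial. The spread between fracture groups also stays in the error term, although a recorded baseline variable could remove it. What is at stake is precision, and how convincing the result looks if the baseline table shows unequal fracture groups.

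**Working it through.** **Inputs from the Protocol article (Power of the trial and sample size):** SD 18, target difference 10 points, α 0.05 (two-sided reproduces the stated number), power 0.80, 51 per group needed, 60 per group enrolled.

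**Assumptions not in the documents:** C2 share 50% (30% to 70% where shown); B2-C2 gap of 5, 10 or 15 Constant points; two age bands.

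**1. The plan's own figure.** n = 2 × (1.960 + 0.842)² × 18² / 10² = 50.9, so 51 per group, as stated. Also 51 / (1 − 0.15) = 60. The point does not alter the sample size.

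**2. Chance imbalance.** With 51 per arm and a 50:50 mix, the SD of the difference in C2 share is √(2 × 0.25 / 51) = 0.099, or 9.9 percentage points.
- P(difference above 10 points) = 0.31
- P(difference above 20 points) = 0.04

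An exact hypergeometric check with 60 per arm and a share of 30% to 70% gives 32% to 36% for 10 points or more, and 3% to 4% for 20 points or more.

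**3. Shift in the unadjusted estimate.** Shift = imbalance × gap.

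| Imbalance | Gap 5 | Gap 10 | Gap 15 |
|---|---|---|---|
| 10 points | 0.5 | 1.0 | 1.5 |
| 20 points | 1.0 | 2.0 | 3.0 |

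At a 10-point gap the shift has an SD of 0.099 × 10 ≈ 1.0 point across trials, against a target difference of 10.

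**4. Variance explained.** Share = 0.25 × gap² / 18².
- Gap 5: 6.25 / 324 = 1.9%
- Gap 10: 25 / 324 = 7.7%
- Gap 15: 56.25 / 324 = 17.4%

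**5. Gain from adjustment at a 10-point gap** (arms taken as nearly balanced on fracture group).
- Unadjusted SE = 18 × √(2/51) = 3.56
- SD within fracture group = √(324 − 25) = 17.29
- Adjusted SE = 17.29 × √(2/51) = 3.42
- Power (normal approximation): 10 / 3.56 − 1.96 = 0.85, giving about 0.80; 10 / 3.42 − 1.96 = 0.96, giving about 0.83

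With the noncentral t distribution the same comparison is 0.79 against 0.82. At gaps of 5 and 15 points, the adjusted power on that basis is 0.80 and 0.86.

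**6. Why not add a stratum.** With two age bands, six hospitals (Method of inclusion) give 6 × 2 × 2 = 24 cells and seven (Abstract) give 28, or 5.0 to 4.3 patients per cell. Adding fracture group doubles this to 48 to 56 cells, with 2.5 to 2.1 patients in each.

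**The case against.** **Leaving a factor out of the strata is not an error.** This stands. Randomisation balances it in expectation, and the t-test remains valid. The SD of 18 comes from a similar fracture population, so chance imbalance is already part of the standard error behind 51 per group.

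**The text does not call B2 versus C2 a confounder.** This largely stands. The Discussion speaks of fracture patterns in the plate procedure, alongside use of a buttress plate, within a paragraph on surgery that cannot be standardised. The Background speaks of displacement and comminution, and severe displacement is required in both groups. No section says that C2 patients score worse. The remark on C-type fractures and screw penetration supports a link to the plate arm but gives no size, so the gap has to be assumed.

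**There are reasons to stratify on age rather than fracture group.** This also stands. The Discussion treats age as important when it defends the lower limit of 65. The radiographic section calls the reproducibility of fracture classification a well-known problem, and age and gender carry no such misclassification.

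**Covariates are commonly left to the statistical analysis plan.** That plan may exist and may adjust; it is not shown. The point is therefore confined to the test that the article does state, which is unadjusted.

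**Conclusion.** The point holds as a modest improvement in precision. As stated, the protocol handles fracture group neither at allocation nor in the comparison of means. At a 10-point gap and a 50:50 mix, using it in the analysis is worth about 3 percentage points of power. At a 5-point gap the gain is under 1 point, and at 15 points about 7. Every one of these figures depends on the assumed gap and mix.

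A reader might infer more: that the trial is biased, that the randomisation is faulty, or that fracture group should replace age as a stratum for the remaining patients. The documents do not support this. There is no bias in expectation, and the likely shift is small beside the 10-point target. Recruitment began in January 2013, so changing strata now would mix two allocation schemes and give up balance on a factor that the protocol values. Nor are the subgroup comparisons invalid: each is still a randomised comparison, and unequal arm sizes within them cost only precision.

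**What to change.** Leave the randomisation unchanged. Replace the unadjusted primary comparison, for all randomised patients, with a prespecified linear model of the Constant score on treatment. The covariates are the fracture group (B2 or C2) recorded before randomisation and the existing stratification factors: age, gender and hospital. Use the pre-allocation classification even if it is later revised, so that the covariate cannot be affected by treatment. If a statistical analysis plan already specifies such a model, the article's Statistics section should be read as superseded by it, and nothing further is needed.

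The cost is a few model terms for variables already collected: one each for fracture group, gender and age, and five or six for hospital. With 102 evaluable patients, this leaves at least 102 − 2 − 9 = 91 residual degrees of freedom. No new data, extra patients or change to the web randomisation are required.

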### Method of inclusion

Patients will be recruited from six collaborating hospitals. An experienced senior consulting orthopaedic surgeon at the local department will classify the radiographs before electronically transmitting them to the study center (OUS Orthopaedic Department), where another consulting orthopedic surgeon experienced in skeletal traumatology will confirm radiographs and inclusion in the trial before randomization and allocation to treatment.

Allocation to treatment will take place after thorough oral and written information to the patient, and signed consent. Electronic randomization will be performed by a dedicated doctor at each hospital, and by means of a secured web-solution made by NTNU WebCRF system, with approval from the OUS Head of Patient Security (https://webcrf.medisin.ntnu.no/client/index.php).

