### Exclusion criteria

Patient younger than 65 years or older than 85 years. Previous history of injury or illness of the injured or contra-lateral shoulder, injuries of other parts of the humerus or the contra-lateral upper extremity, alcohol- or drug abuse, dementia, neurological diseases, or severe cardiovascular or lung diseases that would contraindicate surgery. Patients must understand the Norwegian language and be compliant to rehabilitation and follow-ups. A fracture or severe deformity of the glenoid should not appear in a pre-operative CT-scan of the shoulder.

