### Ethics and safety

The study has been approved by the Regional Committee of Research, Health Region Southeast, Oslo, Norway at November 6^th^ 2012 (Reference 2012/1606).

Patients will be included after thorough oral and written information in accordance with regional ethic committee approval. All patients must give their written consent.

A study specific participant’s number and code referring to their hospitals will identify the participants. Patient name and other identifiable details will not be included in any electronic study data file. Any patient related data transferred between the main study group at OUS and participating sites will be identifiable only by the patients unique study number.

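### Treatment is reported to the project group after every randomisation, and nothing shields the study-centre surgeon who confirms inclusion; if that surgeon sees the messages and blocks are short and fixed, some allocations could be foreseen

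*Protocol article*

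**What the plan says.** Three statements in the protocol article bear on this point.

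- **Sequence (Method of randomization).** The web system allocates "with separate blocks and stratification to age and gender for each collaborating hospital". Block size, and whether it varies, are not given.
- **Feedback (Method of randomization).** Randomising a patient "will generate a coded message to the project group with information of treatment and inclusion number for this hospital".
- **Eligibility (Method of inclusion).** A senior surgeon at the local hospital classifies the radiographs and sends them to the study centre at OUS, "where another consulting orthopedic surgeon experienced in skeletal traumatology will confirm radiographs and inclusion in the trial before randomization and allocation to treatment". The allocation itself is then local: "Electronic randomization will be performed by a dedicated doctor at each hospital, and by means of a secured web-solution made by NTNU WebCRF system".

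Ethics and safety also places the main study group at OUS. The article does not say whether that is the project group, or whether the confirming surgeon belongs to it.

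**The concern.** Central confirmation of eligibility protects against selection only if the person confirming cannot tell which arm comes next. A running record of treatments by hospital, set against a blocked sequence, is the information needed to predict the end of a block. The article sends that record to the project group as routine and states no barrier between its recipients and the confirming surgeon.

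The central reader's judgement is radiographic. The inclusion criteria ask for at least 45° of valgus or 30° of varus, or more than 50% displacement of the head. Under Radiographic evaluation the article itself acknowledges limited observer reproducibility in classifying these fractures. A case near a limit could therefore be read either way. If the next arm were known, the reading could drift with it, and the arms would differ in fracture severity from the start. Neither blinded functional testing nor intention-to-treat analysis corrects selection at entry.

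**Working it through.** **No plan figure is in dispute.** The article quantifies nothing on predictability. Its sample size (difference 10, SD 18, two-sided 5%, power 80%) reproduces: 2 × (1.960 + 0.842)² × 18² / 10² = 50.9, so 51 per group. It plays no part in this point.

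**Inputs from the article.** 120 patients, 1:1. Hospitals: six under Method of inclusion, seven in the Abstract. Strata by age and gender within hospital.

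**Assumptions.**
- Two age classes.
- Patients spread evenly at random over strata.
- Fixed block size B, known to the observer.
- Observer knows every earlier allocation in each stratum.

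**Strata.** 6 × 2 × 2 = 24, or 7 × 2 × 2 = 28. Patients per stratum: 120/24 = 5.0, or 120/28 = 4.3.

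**Chance that an allocation is certain.** In a permuted block of B = 2m, the k-th allocation is certain if one arm is already used up: p(k) = 2 × C(k−1, m) / C(2m, m) for k > m, and 0 otherwise.

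- B = 2: 0, 1
- B = 4: 0, 0, 1/3, 1
- B = 6: 0, 0, 0, 0.1, 0.4, 1

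Averaged over a completed block this is 1/(m+1): 50%, 33% and 25% for blocks of 2, 4 and 6. Those are ceilings, because strata of about five patients leave many blocks unfinished.

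**Expected share.** With S strata and stratum size n distributed Binomial(120, 1/S), the share is (S/120) × Σ p(position of j in its block) × P(n ≥ j), summed over j = 1 to 120. For blocks of 2 this reduces to (S/120) × (120/S − P(n odd))/2, with P(n odd) ≈ 0.5:

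- S = 28: (28/120) × (4.286 − 0.5)/2 = 0.442
- S = 24: (24/120) × (5 − 0.5)/2 = 0.450

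For the other sizes, this formula and a simulation agree to within half a percentage point. The best-guess rates come from the simulation.

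| Block size | Certain, 28 strata | Certain, 24 strata | Best guess right, 28 / 24 strata |
|---|---|---|---|
| 2 | 44% | 45% | 72% / 73% |
| 4 | 24% | 25% | 66% / 67% |
| 6 | 12% | 14% | 62% / 64% |
| 8 | 4% | 6% | 59% / 60% |
| 10 | 1% | 2% | 57% / 57% |

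With unpredictable allocation the best guess is right 50% of the time. Six or seven hospitals makes little difference; block size decides the result.

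**The case against.** The strongest reply is that prediction by the confirming surgeon needs four conditions, none of which the article states:

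1. The surgeon receives or sees the messages. Sharing an institution with the main study group makes this plausible, no more.
2. Blocks are short and of fixed, known size. Block size is often withheld on purpose, and varying blocks may already be in use.
3. The message leaves treatment readable. It is called coded, which may refer to patient identity or may mask the arm.
4. The reader can place earlier patients in their strata. The message is described as carrying treatment and inclusion number, not age or gender, so it would have to be linked to other records.

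All four stand, and they rule out saying that allocations can be foreseen. A condensed article may also leave recipient lists and access rights to the full protocol, and the Abstract attributes the online randomisation to an independent supervisor.

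Two further replies have force. First, the central reader's part is described as confirming radiographs and inclusion. Nothing shows this person weighing criteria such as "Patients must understand the Norwegian language and be compliant to rehabilitation and follow-ups", or general frailty. A reader might infer that frail or unreliable patients could be steered centrally by expected implant; the article does not support that. Second, surgeons cannot be blinded here and a local doctor performs each randomisation, so local staff can learn their own hospital's earlier allocations in any case. The message is one route to prediction, not the only one.

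What remains is not a point about missing detail. The message is a procedure the article specifies. The article states separation of roles for the physiotherapists who test function, the orthopaedic reader of follow-up radiographs and the person reviewing complications, but not for the surgeon confirming eligibility.

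**Conclusion.** The point holds as an avoidable risk to allocation concealment. The stated procedure sends treatment to the project group after every allocation from a blocked, finely stratified sequence, and the person who confirms inclusion beforehand is not shielded from it. If that surgeon sees readable messages, can link them to strata, and knows a short fixed block size, a substantial minority of allocations would be certain in advance: about 44%, 24% and 12% for blocks of 2, 4 and 6. For blocks of 8 to 10 it is only 1–6%.

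A reader might infer that concealment is broken, or that 24% × 120 ≈ 28 patients would be admitted with their arm known. The documents support neither. That count belongs to blocks of 4 with every assumption met, and even then it counts predictable allocations, not biased decisions. Only patients near the radiographic limits would be open to influence. The size of any resulting bias cannot be derived from the article.

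**What to change.** 1. Under Method of randomization, leave treatment out of the automatic message, so that it carries only hospital and inclusion number. Alternatively, send treatment solely to a person with no role in confirming eligibility.
2. Under Method of inclusion, state that the surgeon confirming inclusion has no access to earlier allocations.
3. If not already in place, set randomly varying block sizes in the web system, undisclosed to sites and to the project group. This also limits prediction by local staff, which the first two changes do not touch.

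The cost is a new message template or recipient list, a system setting and one sentence of text. The downside is that the project group no longer sees treatment in real time and must obtain it from the data manager when needed for safety. The planned 18-month review of complications is assigned to an independent researcher and, as described, does not rely on the messages. No sample-size figure changes.
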